#### Implementation

The allocation sequence will be generated by a biostatistician. Subjects will be enrolled in the study and assigned to their intervention group by the project manager.

#### Blinding

Due to the nature of the intervention neither subjects nor staff can be blinded to allocation. The outcomes assessor and data analyst will be blinded after study completion by having the subjects' demographic and intervention group information coded.

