## Abstract

**Background:** Age-related declines in physical function lead to decreased independence and higher healthcare costs. Individuals who meet the endurance and resistance exercise recommendations can improve their physical function and overall fitness, even into their ninth decade. However, most older adults do not exercise regularly, and the majority of those who do only perform one type of exercise, and in doing so are not getting the benefits of endurance or resistance exercise. Herein we present the study protocol for a randomized clinical trial that will investigate the potential for high-intensity interval training (HIIT) to improve maximal oxygen consumption, muscular power, and muscle volume (primary outcomes), as well as body composition, 6-min walk distance, and muscular strength and endurance (secondary outcomes).

**Methods and Analysis:** This is a single-site, single-blinded, randomized clinical trial. A minimum of 24 and maximum of 30 subjects aged 60–75 that are generally healthy but insufficiently active will be randomized. After completion of baseline assessments, participants will be randomized in a 1:1:1 ratio to participate in one of three 12-week exercise programs: stationary bicycle HIIT, stationary bicycle moderate-intensity continuous training (MICT), or resistance training. Repeat assessments will be taken immediately post intervention.

**Discussion:** This study will examine the potential for stationary bicycle HIIT to result in both cardiorespiratory and muscular adaptations in older adults. The results will provide important insights into the effectiveness of interval training, and potentially support a shift from volume-driven to intensity-driven exercise strategies for older adults.

**Clinical Trial Registration:** This trial is registered with ClinicalTrials.gov (registration number: NCT03978572, date of registration June 7, 2019).

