## Methods and Analysis

### Design

This is a single-blinded (outcomes assessor), single-site, randomized control trial. It is a three (group) by two (time) repeated measures factorial design. The overall study is illustrated in Figure 1.

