### Data Management

Data will be entered into the database immediately after each measure is performed by the investigator collecting the measure, and then again at the end of the study by the outcomes assessor. Any incongruous measures will be re-analyzed separately by the outcomes assessor and another blinded investigator. Demographic and intervention group data will be coded and the code will be stored in a locked cabinet unavailable to the outcomes assessor.

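### The single-blinded (outcomes assessor) label does not cover outcomes fixed on the test day: masking starts after study completion, and nothing masks those who run the tests

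*Protocol article*

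**What the plan says.** Two places carry the label. The abstract states: "This is a single-site, single-blinded, randomized clinical trial". The Design section names the masked role: "This is a single-blinded (outcomes assessor), single-site, randomized control trial".

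The Blinding section then narrows this. It says "Due to the nature of the intervention neither subjects nor staff can be blinded to allocation". It goes on: "The outcomes assessor and data analyst will be blinded after study completion", and the means is "by having the subjects' demographic and intervention group information coded".

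Data Management separates two roles. First, "Data will be entered into the database immediately after each measure is performed by the investigator collecting the measure". The data are entered a second time, "and then again at the end of the study by the outcomes assessor". Values that disagree are re-analysed by the outcomes assessor and a second blinded investigator. The code is kept from the outcomes assessor; the article does not say that it is kept from the investigator who collects the measure.

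**The concern.** A reader of the abstract and the Design section will take the blinded outcomes assessor to be the person who obtains the outcome. In the Blinding and Data Management sections, the masked person handles records after the study. Most of the main outcomes here need maximal effort from the subject, and several are run with encouragement from the tester. Such a value is settled when the test ends, and coding the record afterwards cannot change how the test was conducted.

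The stake is what the trial may claim about protection from bias. The dual-benefits hypothesis predicts an ordering of the arms in each domain, so a tester who knows the arm also knows the expected result. The Sample Size section says that the effect sizes could be used to plan a larger trial, so any distortion would carry forward. Treating p-values as descriptive, as that section does, gives no protection, because differential testing would move the estimate itself.

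**Working it through.** There is no figure to reproduce. The check sets the sections side by side.

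**1. When masking starts.** Table 2 places the post-intervention tests at Visits 4 to 6. Masking that begins after study completion begins after those visits. Baseline tests are less exposed, because randomization follows completion of the baseline assessments (Study Timeline, Table 2). The exposure is therefore at the post-intervention tests. Because the Statistical Methods section analyses change or percentage change from baseline, any arm-related distortion at those tests passes into the between-arm comparison.

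**2. Who is masked.** The Blinding section makes no exception for staff who run tests. Data Management treats the collecting investigator and the outcomes assessor as different roles and masks only the second. That testers know the arm is an inference from these two sections, though a direct one. The functional tests add to it: Table 2, note b, places them just before the subject's own session 36, so they share a visit with arm-specific training.

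**3. What each outcome depends on.** Primary and secondary outcomes, from the Outcome Measures section and Table 3:

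| Outcome | Class | What fixes the value | Can later coding protect it? |
|---|---|---|---|
| VO2max | Primary | Effort to the limit, with encouragement; one stopping criterion (signs of severe fatigue) is clearly the tester's judgement | No |
| Isokinetic power | Primary | Maximal effort, six trials; no encouragement stated | No |
| Quadriceps volume | Primary | Off-line tracing of MRI slices | Yes |
| Isometric strength (MVC) | Secondary | Maximal effort, three trials, with encouragement | No |
| Isokinetic fatigue | Secondary | 120 maximal contractions, with encouragement | No |
| 6-min walk | Secondary | Fixed duration, with encouragement | No |
| Total fat mass (DXA) | Secondary | Scanner software | Not effort-dependent |

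**4. Count.** Two of three primary outcomes and three of four secondary outcomes are effort-dependent and fixed on the test day. For these, masked re-entry or reprocessing of the torque signal can guard against errors in transcription or reading, but not against differences in how the test was run.

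**The case against.** The case for the plan has real substance.

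- **The limitation is disclosed.** The Blinding section says openly that staff are unblinded and that the assessor is masked by coding after completion. Read with Data Management, this describes a masked end-of-study assessor, which could be what the Design section means. This stands as a defence against any charge of concealment. It does not repair the label, which is what most readers will carry away and which names no limit.
- **The team may not be uniformly unblinded.** Data Management mentions another blinded investigator, and Randomization specifies an unblinded project manager. The article does not say who runs Visits 4 to 6 or whether they also supervise training, and such detail may sit in a fuller protocol. This stands in part: a reader might infer that the documents state that testers know the arm, and they do not. The point rests on what the article does state, namely that staff cannot be blinded and that the assessor is masked only after completion.
- **Most tests leave the tester little discretion.** This stands. It might be inferred that all these tests combine encouragement with tester-judged stopping. Only the graded exercise test has a stopping judgement, and most of its effort criteria are measured or come from the subject. The other four have fixed trials, contractions or duration. Isokinetic power is exposed through maximal effort alone.
- **The abstract is less specific.** It says single-blinded without naming the outcomes assessor; only the Design section does. The correction to each place should differ accordingly.

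**Conclusion.** The point holds as a mismatch between the stated blinding and the described procedure. The label fits off-line reading, data re-entry, re-analysis of discrepant values and the statistical analysis. It does not fit VO2max, isokinetic power, isometric strength, isokinetic fatigue or the 6-min walk. This rests on one inference: that the staff who cannot be blinded include those who run the post-intervention tests.

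Two stronger readings are not supported. One is that the blinding claim is empty: masking by coding is real for work done after the study, and quadriceps volume, a primary outcome, can benefit from it. The other is that the results will be biased by some stated amount. The documents give no figure for the effect of encouragement or of a tester's knowledge of the arm, so any size would be an invention, and none is given here. The consequence is a limit on what can be claimed, and it should be corrected before results are reported.

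**What to change.** 1. **Relabel.** In the Design section, replace the single-blinded (outcomes assessor) description with a statement that outcome testing is unmasked, while off-line MRI tracing, data re-entry or re-analysis, and statistical analysis are masked to arm. In the abstract, qualify the word single-blinded in the same way. The article does not name who traces the MRI images, so confirm that this person is without the code before claiming it.
2. **Classify.** List each outcome as masked or unmasked, and carry this into the conclusions.
3. **Standardise.** Use one fixed encouragement script for all arms, at baseline and post-intervention tests alike.
4. **Separate roles where existing staffing allows.** Have Visits 4 to 6 run by a staff member who did not train that subject and does not hold the code. The article does not describe staffing, so whether this is feasible is unknown. If it is not, items 1 to 3 still apply.

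Items 1 and 2 are wording changes, and the script costs almost nothing. Sample size, endpoints and analysis stay as they are. The downside is a less favourable blinding statement.

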### Sample Size

In this proof-of-concept, proof-of-mechanism trial, we report sample size estimates based on previous recommended literature (49). A sample size of ~8 subjects per group will detect a moderate effect. Sample size calculation was based on expected effect sizes for the HIIT cycle, MICT cycle, and RT groups for the primary outcomes of V0_2_max and thigh muscle CSA. Consistent with our “dual benefits hypothesis” we assumed, based on the literature, an 8% increase in thigh CSA for both the HIIT and RT groups (50) and 2% increase for the MICT group (51) and common SD across all groups of 4%. With the assumption of a 2-sided test and alpha level of significance equal to 0.05 an *n* = 7/group yields power of 0.83. With respect to VO_2_max we assumed a 32% increase in the HIIT group, a 15% increase in the MICT group, and a 10% increase in the RT group and common SD across all groups of 14% (52). With the assumption of a 2-sided test and alpha level of significance equal to 0.05 an *n* = 8/group yields power of 0.80. In line with other proof-of-concept, proof-of-mechanism trials, no statistical control for type-I error from multiple comparisons will be considered, and *p*-values will be interpreted with care, as descriptive weights of evidence rather than as confirmatory claims. Lastly, this proof of concept, proof of mechanism trial is needed to test the complex interventions proposed, and the effect sizes calculated from this trial could be used to estimate sample size for a future large-scale clinical trial. Accordingly, we plan to enroll an *n* = 8–10 subjects per group.

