### Study Subjects

A minimum of 24 (and up to 30) subjects aged 60–75 years of age that are generally healthy but sedentary will be recruited, enrolled, and randomized in this study (*n* = 8–10 per group). Potential subjects will be recruited from the local community by way of flyers, community events, or emails to individuals who have previously participated in studies with the Ohio Musculoskeletal and Neurological Institute at Ohio University in Athens, Ohio, USA. All interested individuals will complete a pre-screening phone interview, and all that are not ruled ineligible will be invited for in-person screening. Written informed consent will be obtained from each subject in accordance with the Declaration of Helsinki. Ethical Approval for this study has been obtained from the Ohio University Institutional Review Board (protocol number 18-F-55).

Eligible subjects will be insufficiently active. We define “insufficiently active” as not meeting either the endurance or resistance exercise recommendations for older adults, as set forth by the American College of Sports Medicine (ACSM), for three consecutive months. The current ACSM recommendations for endurance training are 150–300 min per week of moderate-intensity activity (perceived exertion of 5–6 on 0–10 scale), or 75–150 min per week of vigorous-intensity activities (perceived exertion of 7–8 on 0–10 scale) (15). The recommendations for resistance training are at least 2 days per week of progressive weight training activities that use the major muscle groups (perceived exertion of 5–8 on 0–10 scale) (15). Additionally, the subjects must not be highly active outside of a structured exercise program (i.e., consistent hard physical labor). They must also have a 6-min walk distance within a normal range for adults aged 60–75. We calculated a normal 6-min walk range by averaging 6-min walk values from multiple studies, plus or minus one standard deviation (45–48). The calculated 6-min walk range for females was 400–675 meters, and for males was 450–725 meters. Table 1 describes inclusion and exclusion criteria in detail. These criteria are designed to recruit a generally healthy, but insufficiently active population, and exclude individuals with poor health and physical function where there could be concerns about a subject's ability to appropriately perform the testing and exercise prescription.

**Table 1 T1:** Inclusion and exclusion criteria.

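### Sample Size: the power of 0.83 at 7 per group does not follow from the printed inputs (0.76 does), and about 8 per group cannot detect a moderate effect

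*Protocol article*

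**What the plan says.** The Sample Size section opens with a general claim: "A sample size of ~8 subjects per group will detect a moderate effect". It then gives two calculations.

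- **Thigh CSA.** The assumed changes are "an 8% increase in thigh CSA for both the HIIT and RT groups (50) and 2% increase for the MICT group (51"), with a "common SD across all groups of 4" percent. The result is n = "7/group yields power of 0.83".
- **VO2max.** Here "we assumed a 32% increase in the HIIT group, a 15% increase in the MICT group, and a 10% increase in the RT group", with a "common SD across all groups of 14" percent. The result is power 0.80 at 8 per group.

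Both calculations carry the same condition: "With the assumption of a 2-sided test and alpha level of significance equal to 0.05". The section applies no multiplicity adjustment and plans 8 to 10 per group. Study Subjects gives the matching total: "A minimum of 24 (and up to 30) subjects aged 60–75 years". Statistical Methods names a one-way ANOVA across the three arms as the test, with Tukey comparisons afterwards and Hedges' g with 95% confidence intervals.

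**The concern.** Every input to the CSA calculation is printed, so the figure can be checked, and it does not come out. The opening sentence about a moderate effect also does not fit the calculations beneath it, which assume differences of more than one standard deviation between the key arms.

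The sensitivity claim is the more important of the two. Under Anticipated Results, the dual-benefits hypothesis expects HIIT to equal RT on muscle outcomes and to equal MICT on endurance outcomes. Half of the predicted pattern would therefore appear as no significant difference. A reader who believes that 8 per group detects moderate effects could take such a result as evidence that no moderate difference exists.

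**Working it through.** **Inputs (Sample Size section).** CSA means 8, 8, 2 with SD 4; VO2max means 32, 15, 10 with SD 14; all in percent. Alpha is 0.05, unadjusted, with equal arms. The test is the three-group one-way ANOVA from Statistical Methods.

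**Formula.** Noncentrality λ = n·Σ(μᵢ − μ̄)²/SD²; df = 2 and 3(n − 1); power = P(F′(λ) > F₀.₉₅). Effect size f = √(Σ(μᵢ − μ̄)²/3)/SD.

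**The stated CSA figure.** The mean is 6, so Σ = 2² + 2² + 4² = 24 and f = √8/4 = 0.707.
- n = 7: λ = 7 × 24/16 = 10.5, df 2 and 18, critical F 3.55, power **0.763**.
- n = 8: λ = 12, df 2 and 21, critical F 3.47, power **0.830**.

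**The stated VO2max figure.** The mean is 19, so Σ = 13² + 4² + 9² = 266 and f = √(266/3)/14 = 0.673. At n = 8, λ = 8 × 266/196 = 10.86 and power is **0.789**, about one point below the stated 0.80.

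**Other methods for CSA at n = 7**

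| Method | Power |
|---|---|
| Two-sided t-test, d = 6/4 = 1.5 | 0.731 |
| The same with pooled ANOVA df | 0.756 |
| Two-sided normal approximation | 0.801 |
| Sidak-adjusted t-test | 0.578 |
| Contrast of HIIT + RT against MICT | 0.865 |
| One-sided t-test | 0.841 |
| Large-sample chi-square version of the ANOVA | 0.835 |

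Only the last two come within two points of 0.83. The one-sided test contradicts the stated two-sided test. The chi-square version gives 0.848, not 0.80, for VO2max at n = 8.

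**Rounded inputs.** An SD of 3.7% would print as 4%. It gives ANOVA power 0.829 at n = 7.

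**Power at the planned size (ANOVA)**

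| n per group | CSA | VO2max |
|---|---|---|
| 8 | 0.830 | 0.789 |
| 9 | 0.880 | 0.844 |
| 10 | 0.916 | 0.886 |

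**What 8 to 10 per group can detect.** The assumed pairwise effects are d = 1.5 (CSA, HIIT against MICT), 17/14 = 1.21 (VO2max, HIIT against MICT) and 22/14 = 1.57 (VO2max, HIIT against RT).

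| Quantity | n = 8 | n = 10 |
|---|---|---|
| f for 80% power (ANOVA) | 0.68 | 0.60 |
| d for 80% power (two-group t-test) | 1.51 | 1.32 |
| Power at f = 0.25 | 0.16 | 0.20 |
| Power at d = 0.5 | 0.15 | 0.19 |
| Power at f = 0.4 | 0.35 | 0.44 |

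The values f = 0.25 and d = 0.5 are the usual convention for a medium effect, and f = 0.4 for a large one. The article does not define the term.

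**The case against.** The strongest reply is that the n = 7 figure decides nothing. No arm is planned at 7; VO2max sets the minimum of 8, and at 8 to 10 per group the CSA power is at or above the stated 0.83. This stands. A reader might infer that the trial is undersized, and the article does not support that.

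Second, it is tempting to say that 0.83 simply belongs to n = 8. The match is exact, and the same method nearly reproduces the VO2max figure, but this remains an inference. The section does not name the test behind its powers, and an unrounded SD near 3.7% would give 0.83 at n = 7. What can be said is that the figure does not follow from the inputs as printed.

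Third, a reader might infer that the section promises a spare subject per arm, or that its power holds only if nobody is lost. The text mentions no spare, and the second statement applies only at the minimum of 24. With 10 randomised per arm and two lost, 8 remain and the powers are 0.83 and 0.79. Powers at 7 per arm would be added content, not the correction of an error.

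Fourth, the word moderate follows a reference to cited literature that is not available here, and the actual means and SDs are printed directly below it. The article also treats p-values as descriptive and reports Hedges' g with confidence intervals, which would show that a moderate difference had not been excluded. This lessens the risk of misreading. It does not make the sentence true: at 8 per group, even a conventionally large effect (f = 0.4) has power of only 0.35.

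**Conclusion.** Two statements need correcting. The CSA power at 7 per group is 0.76 from the printed inputs, not 0.83, an overstatement of about 7 points (0.83 − 0.763 = 0.067). The claim that about 8 per group detects a moderate effect contradicts the section's own assumptions: the effect detectable with 80% power at that size is f of about 0.68, or d of about 1.5.

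The first conclusion assumes that the power refers to the planned ANOVA and that the inputs are as printed. The figure of 0.16 for a moderate effect assumes f = 0.25. The error lies in one reported figure and in the sensitivity claim. It does not affect the enrolment target, the analysis or the conduct of the trial.

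**What to change.** In the Sample Size section:

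1. Restate the CSA power as 0.76 at 7 per group and 0.83 at 8 per group. If the original calculation used an unrounded SD that yields 0.83 at 7, print that SD instead. Name the test that the powers refer to.
2. Replace the moderate-effect sentence with the size detectable at 80% power: f of about 0.68 at 8 per group and 0.60 at 10, or a two-group d of about 1.5 and 1.3.

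The cost is a change of wording. Sample size, design and analysis stay as they are; the stated sensitivity becomes less favourable.

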### Statistical Methods

The three intervention arms (HIIT, MICT, and RT) will be compared against each other for all primary analyses. For total fat mass and the primary and secondary knee extensor-related outcomes (isokinetic power, muscle volume, MVC, and isokinetic fatigue), we will compute a percentage change from baseline to 12 weeks. For absolute and relative VO_2_max and 6-min walk distance we will compute absolute change from baseline to 12 weeks. We will test differences in group means using one-way ANOVA with Sidak option in SPSS v. 25.0. Tukey *post hoc* tests will be performed if significant differences exist, alpha level set at 0.05. Additionally, as this is a proof-concept, proof of mechanism trial we will calculate effect sizes between groups using the corrected effect size Hedge's g with 95% confidence intervals for small sample sizes (65).

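### The plan disclaims multiplicity control but names both Sidak and F-gated Tukey for the same three pairwise comparisons; under either, the hypothesised superiority contrasts lose about 13 to 16 points of power at 8 per group (8 to 11 at 10)

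*Protocol article*

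**What the plan says.** Three parts of the protocol article bear on this.

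- **Sample Size.** It states that "no statistical control for type-I error from multiple comparisons will be considered" and that p-values will be read descriptively, not as confirmation. It gives power of 0.83 for thigh CSA at 7 per group and 0.80 for VO2max at 8 per group, "With the assumption of a 2-sided test and alpha level of significance equal to 0.05", without naming the test.
- **Statistical Methods.** "The three intervention arms (HIIT, MICT, and RT) will be compared against each other for all primary analyses". Group means are to be tested by "one-way ANOVA with Sidak option in SPSS v. 25.0". Tukey post hoc "tests will be performed if significant differences exist, alpha level set at 0.05". Hedges' g with 95% confidence intervals is reported as well.
- **Anticipated Results, The Dual-Benefits Hypothesis.** On endurance measures HIIT is expected to exceed RT and match MICT. On muscular measures it is expected to exceed MICT and match RT. The superiority comparisons are therefore fixed in advance.

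**The concern.** Sidak and Tukey both control familywise error over a set of pairwise comparisons. Statistical Methods names both for the same three comparisons, puts Tukey alone behind a significance gate, and does not say which result is reported. Sample Size appears to rule out both. As written, one comparison on one outcome can carry an unadjusted, a Tukey or a Sidak p-value, and the text can be cited for each.

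Two things are at stake. First, a borderline comparison could be called positive or negative depending on a rule the plan does not fix. Second, the quoted powers are not tied to the comparisons that carry the superiority half of the hypothesis, and under either adjusted rule those comparisons have less power than the section suggests.

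**Working it through.** **Inputs (Sample Size).** Thigh CSA: "an 8% increase in thigh CSA for both the HIIT and RT groups", 2% for MICT, SD 4%. VO2max: 32% HIIT, 15% MICT, 10% RT, SD 14%. Two-sided alpha 0.05; 8 to 10 per group planned. Superiority contrasts (The Dual-Benefits Hypothesis): HIIT versus MICT on muscle, a difference of 8 − 2 = 6 points; HIIT versus RT on VO2max, a difference of 32 − 10 = 22 points.

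**Step 1. The plan's own power figures.** For a one-way ANOVA with three groups of n, the noncentrality is λ = n·Σ(μᵢ − μ̄)²/SD², on 2 and 3(n − 1) degrees of freedom.

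- VO2max: the mean is 19 and the squared deviations are 169 + 16 + 81 = 266. At n = 8, λ = 8 × 266/196 = 10.86 and power is 0.789. The stated 0.80 is close to this.
- CSA: the mean is 6 and the squared deviations are 4 + 4 + 16 = 24. At n = 7, λ = 7 × 24/16 = 10.5 and power is 0.763, not the stated 0.83. At n = 8, λ = 12 and power is 0.830.

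At n = 7, a large-sample chi-square approximation (0.835) or a one-sided two-sample t-test (0.841) comes near 0.83. The planned two-sided ANOVA does not.

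**Step 2. Critical values for one pairwise comparison, n = 8, df = 3 × 7 = 21.**

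- Unadjusted: t(0.975; 21) = 2.080.
- Tukey: studentised range q(0.95; 3, 21)/√2 = 3.565/1.414 = 2.521.
- Sidak for three comparisons: per-comparison alpha 1 − 0.95^(1/3) = 0.01695, giving 2.594.

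An observed t of 2.5 on 21 df gives p = 0.021 unadjusted, 0.052 Tukey and 1 − (1 − 0.0208)³ = 0.061 Sidak.

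**Step 3. Power for the superiority contrasts.** The noncentral t has parameter δ = difference/(SD·√(2/n)) with the pooled three-arm variance. At n = 8, δ = 6/(4 × 0.5) = 3.00 for CSA and 22/(14 × 0.5) = 3.14 for VO2max. The F-gated column was simulated with 400,000 trials per setting.

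| Contrast | n per group | Unadjusted | Tukey, no gate | F then Tukey | Sidak |
|---|---|---|---|---|---|
| HIIT vs MICT, CSA | 8 | 0.816 | 0.683 | 0.679 | 0.658 |
| HIIT vs RT, VO2max | 8 | 0.850 | 0.729 | 0.720 | 0.705 |
| HIIT vs MICT, CSA | 10 | 0.898 | 0.803 | 0.80 | 0.784 |
| HIIT vs RT, VO2max | 10 | 0.923 | 0.842 | 0.836 | 0.826 |

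**Step 4. Size of the loss.** At n = 8, F then Tukey costs 0.816 − 0.679 = 13.7 points on CSA and 0.850 − 0.720 = 13.0 on VO2max; Sidak costs 15.8 and 14.5. At n = 10 the losses run from about 8 points (0.923 − 0.842, Tukey on VO2max) to 11 (0.898 − 0.784, Sidak on CSA). At n = 8 the gate adds only 0.683 − 0.679 = 0.4 points to Tukey on CSA and 0.729 − 0.720 = 0.9 on VO2max, so the adjusted critical value does nearly all the damage.

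**The case against.** The best defence is that the Sample Size sentence means no adjustment across the several outcomes, while Statistical Methods deals with the three arms within one outcome. The sentence does not say this, but the reading is possible and would remove the conflict between the two sections. It would not remove the conflict inside Statistical Methods, where two adjustments remain for the same comparisons. On that reading the gap is narrow: critical values of 2.52 and 2.59, and about 2.5 points of power between ungated Tukey and Sidak at n = 8.

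The consequences are also limited. P-values are declared descriptive, Hedges' g and its intervals do not depend on the adjustment, and the data analyst is to work with coded groups, which reduces the scope for choosing a rule after seeing results. All of that stands. Even so, a descriptive p-value has to be one defined number, and the section still sets alpha at 0.05 and makes Tukey conditional on significance.

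An all-pairs procedure is not wrong in itself either, since the plan says that all three arms are compared with each other. Planned contrasts fit the named hypothesis better and agree with the Sample Size stance, but this is a choice between defensible rules.

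A reader might infer that both quoted powers are omnibus-F figures. The documents do not support that: no test is named, and the CSA figure at 7 per group does not match the F-test. A reader might also multiply the two contrast powers into a joint power for the dual-benefits hypothesis. That would leave out the comparisons in which HIIT is expected to match the other arm and the third primary outcome, isokinetic power, and it would need an independence assumption that the documents do not give.

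**Conclusion.** The inconsistency is real. Statistical Methods names two familywise procedures for one set of comparisons and does not say which is reported; read literally, Sample Size rules out both. Against unadjusted pairwise tests, the adjusted rules cost the superiority contrasts about 13 to 16 points of power behind the F-test or with Sidak at 8 per group, and about 8 to 11 points at 10 per group. It would overstate the case to apply the larger range to the whole planned sample size or to blame the F-gate.

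The figures assume the Sample Size means and SDs, equal groups, normal data and the pooled three-arm variance. They also carry percentage changes in CSA and VO2max over to an analysis that uses percentage change in muscle volume and absolute change in VO2max. Because the p-values are descriptive, this is a point that should be fixed, not one that undermines the trial.

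**What to change.** State one rule and its scope, including whether the Sample Size sentence covers comparisons between arms, between outcomes, or both. In line with that section:

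- Report the pairwise contrasts named in The Dual-Benefits Hypothesis from the three-arm model, unadjusted at two-sided 0.05 with 95% confidence intervals, and without requiring a significant F-test.
- Delete the Sidak option. If Tukey is kept, confine it to comparisons that the hypothesis does not name.
- Report the comparisons in which HIIT is expected to match another arm as estimates with 95% confidence intervals, and say that a non-significant difference will not be read as equality.
- In Sample Size, name the test behind each power figure, reconcile 0.83 at 7 per group with the planned analysis, and quote contrast power: 0.82 for CSA and 0.85 for VO2max at 8 per group.

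Only wording changes; design and sample size stay as they are. The price is no familywise control for the named contrasts, which Sample Size already accepts.
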